## E4. Endpoint Adjudication

A consensus of two reviewers ([name], [name]) will adjudicate elements required to measure the occurrence of all MACE endpoints. Reviewers will adjudicate return visits to the ED or readmissions within the ED are cardiac related if this unclear based on preliminary review by project staff. To make these assessments, reviewers will be provided the participant’s index and discharge records, records obtained from follow-up including claims data when available, and project definitions. Records will have patient identifiers removed. Reviewers will complete a reviewer outcome form recording the occurrence of safety endpoints, which will be stored in our secured electronic database. Any disagreements will be settled by consensus between the two reviewers, or the involvement of a third reviewer ([name]).

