Paramedics will use a worksheet to obtain the historical and clinical data needed to calculate a HEART score. This will include performing POC troponin testing. This is within the scope of practice of paramedics who routinely perform venipuncture and POC testing on acutely ill patients. Furthermore, the feasibility of performing POC troponin analyses in a moving ambulance has been previously established. Given the paramedic’s need to use the POC troponin value for HEART score calculation they cannot be blinded to the troponin results. However, during this pilot, they will not deviate from their normal chest pain triage and destination plans based on the results. The routine chest pain triage and destination plans for these EMS counties include obtaining an IV, ECG, and the administration of aspirin, nitroglycerin, and supplemental oxygen. Also, during this pilot, i-STAT troponin and HEART Score results will not be used to determine or alter the patient’s transportation destination.

Since paramedics are not blinded to POC troponin results we will not prevent them from sharing their i-STAT troponin results with the ED care team as part of their typical transfer of care reports. However, they will do so using a study specific form, which clearly states that this POC troponin value is for study purposes only and is not to be used to determine a patient’s clinical care. We will train ED nurses and providers that EMS POC troponin results are part of a pilot, should not be acted on clinically at this time, and require confirmation with a core-lab troponin. While the ED care team will receive report on the POC troponin results (as well as the patient’s clinical features and ECG, as part of a normal EMS verbal report), the ED care team will remain blinded to paramedics’ HEART Scores to allow evaluation of agreement between paramedic and ED provider risk assessments. HEART Score calculation by the ED provider is part of the standard ED care for patients with acute chest pain presenting to the WFBMC ED, which will facilitate assessment for agreement. Paramedic POC troponin results and HEART Scores will not become part of the patient’s medical record.

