## E. Project Procedures

## E1. Clinical Data Collection

For quality assurance data collection, participants will be identified retrospectively and data will be collected electronically using EHR (EMS records, and WFBH medical records) and via telephone follow-up calls.

Paramedics will use a worksheet to obtain the historical and clinical data needed to calculate a HEART score and this will include recording the POC troponin results. This worksheet will be an investigational record integrated into their normal reporting workflow. Data entered on this worksheet will be abstracted retrospectively. Data obtained will include demographic information (age, gender, race, ethnicity), date and time elements, characteristics of chest pain, ECG interpretation, cardiac risk factors (such as, prior coronary artery disease, smoking, hypertension, diabetes, hyperlipidemia, etc), POC troponin value, and the HEART score.

Since all participants will be transported to WFBMC ED, where the HEART Pathway is part of standard care, we will use the electronic medical record (EMR) to obtain ED physician HEART Score assessments and WFBMC troponin results. These data will be compared to paramedic assessments for determination of inter-observer agreement and correlation. We will also use the EMR to track index outcomes and 30 day events that occur within the WFBH system. Data collected from the WFBH EMR will include patient demographics, history and physical examination data, past medical history, cardiovascular risk factors, ECG results, laboratory results, HEART score and HEART Pathway assessments, ED and discharge diagnoses, disposition, index visit length of stay, objective cardiac testing at the index visit or within 30 days, recurrent ED visits, re-admissions, coronary revascularization, and MI or death within the follow-up period.

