**F. Statistical Plan**

F1. Overview

The primary concept of the PARA-HEART project is to evaluate whether paramedics can be taught to calculate a HEART score accurately with acceptable intra-observer reliability (when compared to ED physician assessments). This project is a clinical pilot study in order to generate data to support a larger and non-observational implementation. If we are able to show that these scores can be reliably predict MACE and agree with ED physicians assessments, then we can start using the HEART score in the pre-hospital setting to alter care and transport triage and destination plans.

F2. Sample Size and Power

The PARA-HEART project is a clinical pilot study in which we hope to demonstrate that paramedics are able to achieve 98% sensitivity for the detection of MACE. To achieve a sensitivity of 98% with a lower bound of the 95% confidence interval that exceeds 90% we will need at least 50 patients with MACE events. Assuming a 10% MACE rate among our chest pain population,[^4-7^](#_ENREF_4) to include 50 patients with adverse events we will need a total sample size of 500 patients.

F3. Analysis Plan and Statistical Methods

The percentage of patients identified by paramedics using the HEART Score with POC troponin testing as high- and low-risk, the sensitivity, specificity, and positive and negative predictive values, positive and negative likelihood ratios, and accuracy for MACE will be calculated. Corresponding 95% exact binomial confidence intervals will be computed.

The proportion of patients receiving objective cardiac stress testing, cardiac catheterization, myocardial infarction, or cardiac death during the index hospitalization will be estimated for subjects classified as high and low risk by ED physicians and compared with those classified as high and low risk by paramedic assessment. Cardiac-related ED visits and readmission to the hospital will be calculated at 30 day follow-up. LOS will be reported using descriptive statistics, including median and inter-quartile range as this outcome tends to have a nonparametric distribution.

HEART scores calculated by the blinded primary ED provider will be compared to the HEART scores obtained by the paramedics. Raw percent agreement and kappa scores will be determined to assess intra-observer reliability. A kappa of >0.75 will be defined as excellent agreement, 0.60-0.74 will be defined as acceptable agreement, and <0.59 will be defined as unacceptable agreement.

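### Adjudication packets lose only patient identifiers, so the ED HEART class would normally stay visible; the main exposure is the F3 outcome comparison of ED and paramedic classes

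*Protocol*

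**What the plan says.** E4 has two reviewers adjudicate by consensus, with a third available, whatever is needed to establish each MACE endpoint. They receive "index and discharge records, records obtained from follow-up including claims data when available, and project definitions". The only masking step is "Records will have patient identifiers removed". Elsewhere, blinding is described only for the ED team, toward the paramedic's score (A1 Methods, D1, D4).

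The ED rating is in the hospital record. A1 Methods says "HEART Score calculation by the ED provider is part of the standard ED care for patients with acute chest pain". In E1 the project states "we will use the electronic medical record (EMR) to obtain ED physician HEART Score assessments and WFBMC troponin results", and the items abstracted from that record include "HEART score and HEART Pathway assessments, ED and discharge diagnoses".

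The paramedic rating is handled differently. A1 Methods keeps the paramedic HEART score and prehospital troponin out of the medical record, and D4 does the same for the worksheet. The troponin value is, however, passed to the ED team at handover on a study form.

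Adjudicated MACE is the reference standard for all the accuracy measures listed in E2. F3 also estimates index-visit stress testing, catheterization, MI and cardiac death for patients "classified as high and low risk by ED physicians and compared with those classified as high and low risk by paramedic assessment".

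**The concern.** A reference standard should be judged without knowledge of the classification it will be used to assess. If reviewers can see that the ED called a patient low or high risk, an equivocal case may be pulled toward that class. The components open to judgement are MI, where troponin must be joined to symptoms, ECG or imaging, and the cause of an unexpected death.

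Two analyses could be touched. The first is the F3 comparison by ED class and paramedic class, where one of the two classifications would be visible to those judging its outcomes and the other would not. The second is paramedic sensitivity, because the ED and paramedic scores share the same five components and the protocol hypothesises a kappa above 0.60 between them.

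**Working it through.** **Who can see what.** Setting E4 beside E1 and A1 Methods:

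- ED HEART score and Pathway assessment: in the electronic record; no redaction stated. Normally visible in an index record stripped of identifiers.
- Paramedic score and worksheet: not in the medical record. Not normally visible.
- Prehospital troponin: kept out of the record, but told to ED staff. It could be repeated in a free-text note; no section says that it is.

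**Plan's own figure.** F2 takes 50 MACE at a 10% rate: 50 / 0.10 = 500 patients, which reproduces. F2 targets 98% sensitivity with a lower 95% bound above 90%; F3 specifies exact binomial intervals.

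**Direction.** Assume reviewers lean toward the ED class on one equivocal event. Take paramedic sensitivity of 48/50 = 96.0% (exact 95% CI 86.3 to 99.5) as the starting point. The two missed events are an assumption.

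| ED class | Paramedic class | Leaning call | Paramedic sensitivity | Change (points) | ED rating |
|---|---|---|---|---|---|
| Low | Low | True event rejected | 48/49 = 97.96% | +1.96 | one miss removed |
| Low | High | True event rejected | 47/49 = 95.92% | -0.08 | one miss removed |
| High | High | Non-event accepted | 49/51 = 96.08% | +0.08 | one true positive added |
| High | Low | Non-event accepted | 48/51 = 94.12% | -1.88 | one true positive added |

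The ED rating gains in every row. The paramedic rating gains where the classes agree and loses where they disagree. The F3 comparison therefore has a predictable tilt, and paramedic sensitivity does not.

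**Size for the primary measure.** In the first row the exact interval for 48/49 is 89.1% to 99.9%. The estimate of 97.96% is just under 98%, and the lower bound is under 90%. Only if both assumed misses were rejected would the result be 48/48 = 100% (92.6 to 100) and clear both criteria. The protocol does not say how many events would be equivocal, so these are illustrations and not estimates of bias.

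**What is not touched.** Percent agreement and kappa compare two scores and use no adjudicated outcome. Stress testing and catheterization, two of the four F3 items, are not MACE endpoints. Revascularization is largely a matter of record.

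**The case against.** The strongest reply is that the primary accuracy aim concerns the paramedic score, and the protocol already keeps that score and its troponin out of the record. This stands: the index test is largely masked, and only an indirect route through the ED score remains.

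Second, no section says that the ED score is in the packet. E1 lists what project staff abstract, E4 names record types, and G3 and G5 leave procedural detail to a manual that is not shown. This also stands in part. Visibility is an inference, though nothing in the protocol contradicts it, and E4 does specify what is redacted.

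Third, there is limited room for judgement. MI needs a troponin rise or fall with a value above the 99th percentile, and nearly everyone enrolled has symptoms that could count as ischemic. Unexpected death is confined to 24 hours from onset without evidence of another cause. This limits the size but does not remove the problem, since E4 itself provides for disagreement between reviewers.

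Fourth, a reviewer who needs the ECG, troponin and history can partly rebuild the class. That is correct, and it limits what the remedy may claim.

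A reader might also infer that reviewers see the paramedic score, that agreement between raters is biased, that sensitivity is necessarily inflated, or that one reclassified event would meet the target. The protocol supports none of these. The paramedic score is outside the record, kappa uses no outcome, the direction depends on concordance, and 48/49 misses both criteria.

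**Conclusion.** The point holds in a limited form. As written, E4 leaves reviewers unmasked to the ED classification, assuming that the index record they receive includes the ED score that E1 says is held there. The principal consequence is a possible tilt toward the ED rating when F3 sets index MI and cardiac death by ED class against the same outcomes by paramedic class. The effect on paramedic sensitivity is secondary, of either sign, and in the illustration at most about 2 points per reclassified event with about 50 MACE. The number of equivocal events is unknown, so no overall bias can be stated. This is worth correcting because the correction is small, not because the primary result is shown to be wrong.

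**What to change.** In E4, extend the planned redaction to the recorded ED HEART score, the HEART Pathway class and any mention of the EMS troponin or the paramedic score, including in free-text notes. State that adjudicators are not given either rater's risk classification. Leave the hospital ECGs, core-lab troponins, history and imaging in the packet, because the MI definition needs them. For that reason, do not describe the reviewers as fully masked.

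The cost is some extra redaction time per packet, mostly in searching free-text notes. E4 does not say whether packets are prepared for every participant or only for possible events, so the total cannot be given. No added staff, visits or data are required.

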**F. Statistical Plan**

F1. Overview

The primary concept of the PARA-HEART project is to evaluate whether paramedics can be taught to calculate a HEART score accurately with acceptable intra-observer reliability (when compared to ED physician assessments). This project is a clinical pilot study in order to generate data to support a larger and non-observational implementation. If we are able to show that these scores can be reliably predict MACE and agree with ED physicians assessments, then we can start using the HEART score in the pre-hospital setting to alter care and transport triage and destination plans.

F2. Sample Size and Power

The PARA-HEART project is a clinical pilot study in which we hope to demonstrate that paramedics are able to achieve 98% sensitivity for the detection of MACE. To achieve a sensitivity of 98% with a lower bound of the 95% confidence interval that exceeds 90% we will need at least 50 patients with MACE events. Assuming a 10% MACE rate among our chest pain population,[^4-7^](#_ENREF_4) to include 50 patients with adverse events we will need a total sample size of 500 patients.

F3. Analysis Plan and Statistical Methods

The percentage of patients identified by paramedics using the HEART Score with POC troponin testing as high- and low-risk, the sensitivity, specificity, and positive and negative predictive values, positive and negative likelihood ratios, and accuracy for MACE will be calculated. Corresponding 95% exact binomial confidence intervals will be computed.

The proportion of patients receiving objective cardiac stress testing, cardiac catheterization, myocardial infarction, or cardiac death during the index hospitalization will be estimated for subjects classified as high and low risk by ED physicians and compared with those classified as high and low risk by paramedic assessment. Cardiac-related ED visits and readmission to the hospital will be calculated at 30 day follow-up. LOS will be reported using descriptive statistics, including median and inter-quartile range as this outcome tends to have a nonparametric distribution.

HEART scores calculated by the blinded primary ED provider will be compared to the HEART scores obtained by the paramedics. Raw percent agreement and kappa scores will be determined to assess intra-observer reliability. A kappa of >0.75 will be defined as excellent agreement, 0.60-0.74 will be defined as acceptable agreement, and <0.59 will be defined as unacceptable agreement.

*Post-Hoc Analysis of Troponin Cut Points:* For the clinical pilot, paramedics will use a cut point of 0.08 ng/mL, which corresponds to the published 99^th^ percentile upper reference limit for the assay. However, following completion of the pilot we will analyze different troponin cut points (including 0.04 ng/mL) used alone or in combination with the HEART score to find the combination with the greatest accuracy (area under the curve in a receiver operator curve).

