## A2. Primary Hypotheses

- Paramedics using the HEART score and Abbott’s i-STAT^®^ point-of-care troponin assay in the pre-hospital setting will achieve 98% sensitivity and negative predictive value for MACE during the index visit and at 30 days in patients with symptoms concerning for ACS.
- Inter-rater reliability (kappa) for HEART scores calculated by ED physicians in a hospital setting and paramedics in the pre-hospital setting using Abbott’s i-STAT^®^ point-of-care troponin assay will exceed 0.60.

##

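### The primary hypothesis is 98% sensitivity, but the study is sized for a lower bound above 90%, and 50 events can meet 98% only as a point estimate

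*Protocol*

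**What the plan says.** Section A2 of the protocol states the first primary hypothesis: paramedics using the score with the point-of-care assay "will achieve 98% sensitivity and negative predictive value for MACE during the index visit and at 30 days". Specific Aim 2, in the abstract and again in section C, uses the same 98% for the same two measures. None of these places says whether 98% is an observed proportion or a value that the confidence interval must exclude.

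Section F2 repeats the target for sensitivity alone: "we hope to demonstrate that paramedics are able to achieve 98% sensitivity for the detection of MACE". Its next sentence gives the basis for the sample size: "To achieve a sensitivity of 98% with a lower bound of the 95% confidence interval that exceeds 90% we will need at least 50 patients". The total follows from "Assuming a 10% MACE rate among our chest pain population", so that "we will need a total sample size of 500 patients". No sizing is given for NPV.

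Section F3 names the interval method for all accuracy measures: "Corresponding 95% exact binomial confidence intervals will be computed". It gives no success rule for sensitivity or NPV, although it does grade the kappa of the second primary hypothesis into bands. Section F1 says that if the scores prove reliable predictors and agree with the ED physicians, "then we can start using the HEART score in the pre-hospital setting to alter care and transport triage and destination plans".

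**The concern.** Two numerical standards are attached to one primary hypothesis: 98% in A2, Aim 2 and the opening of F2, and 90% in the sizing sentence of F2. They are different quantities, and the protocol does not say which one a positive conclusion rests on. Sensitivity of 98% cannot be shown with confidence from 50 events, whatever the result. That leaves the point-estimate reading, which a score with true sensitivity clearly below 98% can meet fairly often.

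At stake is what the study may claim. A result of 49/50 could be reported as 98% achieved while its exact interval reaches below 90%. NPV carries the same 98% label with neither a planned denominator nor a criterion.

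**Working it through.** **Inputs.** From F2: anticipated sensitivity 98%, lower-bound benchmark 90%, 50 events, MACE rate 10%. From F3: 95% exact binomial (Clopper-Pearson) intervals. F3 does not state sidedness; two-sided is taken as the default.

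**1. The plan's own figures.** 50 / 0.10 = 500, so the total reproduces. The step to 50 events does not reproduce under F3's method. The exact lower bound exceeds 90% only if the chance of a result at least as good, at a true sensitivity of 0.90, is below 0.025.
- 49/50: 0.90^50 + 50 × 0.10 × 0.90^49 = 0.005 + 0.029 = 0.034, which is above 0.025. The lower bound is 89.4% (interval 89.4% to 99.9%).
- 50/50: 0.90^50 = 0.005. The lower bound is above 90%.
- 53/54: 0.90^54 + 54 × 0.10 × 0.90^53 = 0.0034 + 0.0203 = 0.0237, which is below 0.025. The lower bound is 90.1%, and 54 is the smallest count that passes with one miss (54 / 0.10 = 540 patients).

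So at 50 events only 50/50 clears 90%. Its probability at a true 98% is 0.98^50 = 0.36.

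Other methods at 49/50 give these lower bounds: Wald 94.1%, Jeffreys 91.0%, one-sided 95% exact 90.9%, Wilson 89.5%, Agresti-Coull 88.5%. The sentence in F2 is therefore true under some methods, but not under the two-sided exact one.

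**2. Can 50 events show 98% with confidence?** With no misses the two-sided exact lower bound is 0.025^(1/n).
- n = 50: 0.025^(1/50) = 0.929. One-sided 95%: 0.05^(1/50) = 0.942.
- For a lower bound of at least 0.98 with no miss: n = 183, about 1,830 patients at 10% MACE. With one miss, 277 events are needed. One-sided with no miss, 149.

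Chance variation in the event count does not alter this: 183 events among 500 patients would be a MACE rate of 36.6%, against the 10% assumed.

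**3. 98% as a point estimate.** An observed 98% or more in 50 events means at most one miss. For true sensitivity s the probability is s^50 + 50(1 − s)s^49:

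| True sensitivity | P(at most 1 miss in 50) |
|---|---|
| 98% | 0.74 |
| 95% | 0.28 |
| 93% | 0.13 |
| 90% | 0.03 |

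**4. NPV.** Its denominator is the number of low-risk patients, L, which the protocol does not give. Assume L = 150 to 250 of 500.
- Observed NPV of 98% allows 0.02 × L misses: 3, 4 or 5 for L = 150, 200 or 250. With 50 events that is sensitivity of 47/50, 46/50 or 45/50, that is 94%, 92% or 90%.
- Exact lower bound with no misses: 97.6% (L = 150), 98.0% (L = 183), 98.2% (L = 200), 98.5% (L = 250). With one miss it is below 98% at every L examined (100 to 250).

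**The case against.** The strongest reply is that F2 is ordinary precision sizing. One sentence gives an expected value (98%) and a minimum precision (lower bound above 90%), which is a coherent design for a self-described pilot, and F3 attaches an interval to every measure. That reading is reasonable, but A2 and Aim 2 do not contain it, and F2 itself introduces the calculation with the verb *demonstrate*. Even on that reading, the stated precision is not delivered at 49/50 by the interval F3 prescribes.

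A formal success rule may be in a statistical analysis plan that is not shown. This is why the missing rule alone is not the complaint. The hypothesis, the sizing benchmark and the interval method all stand in the protocol and do not agree with one another there.

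Two stronger readings are tempting and are not supported. First, a reader might infer that 98% is the threshold for changing EMS care. F1 and A3 set only qualitative conditions (reliable prediction and agreement with ED physicians; feasibility and accuracy established), and neither names 98%. Second, a reader might infer that the study cannot demonstrate 98% NPV either. NPV does not depend on the 50 events: no misses among at least 183 low-risk patients (36.6% of 500) would put its exact lower bound at 98% or above. Nor is it a contradiction that 98% NPV and 98% sensitivity allow different numbers of misses, since they are different measures. The NPV point is only that its 98% has no sizing and no criterion.

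**Conclusion.** The concern holds as a mismatch between the claim and the sizing. With the planned 50 events, sensitivity of 98% can be met only as an observed proportion. That criterion passes with probability 0.74 when the truth is 98%, and still 0.28 at 95% and 0.13 at 93%. The most favourable possible result supports a sensitivity above 92.9%, and one miss supports about 89%. The 90% benchmark in F2 is itself missed at 49/50.

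The lower bounds rest on two-sided 95% exact intervals. On a one-sided 95% exact bound 49/50 would clear 90% (90.9%), but 50/50 would still fall short of 98% (94.2%). The probabilities assume exactly 50 events and independent classifications. The NPV illustration rests on an assumed low-risk share.

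**What to change.** - **A2, Aim 2 and F2:** describe 98% as the anticipated point estimate for sensitivity and replace the verb *demonstrate*. Limit the positive sensitivity conclusion to what the exact 95% lower bound supports, with 90% as the benchmark.
- **F2:** correct the stated property. Either raise the event count to 54, which allows one miss (about 540 patients at 10% MACE), or keep 50 and state that one miss gives a lower bound of about 89%, and that only 50/50 exceeds 90% (probability 0.36 at a true 98%). State that the interval is two-sided.
- **NPV:** report it as an estimate with its exact interval rather than as a second 98% pass mark.

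If the 50 events are kept, this costs protocol wording only. Raising the count to 54 adds about 40 patients. In both cases the claim open to the study becomes less favourable: a lower bound judged against 90% instead of 98% achieved.

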**B. Background**

B1. Prior Literature and Studies

Coronary heart disease affects 15.8 million people in the US[^1^](#_ENREF_1) and represents a major public health dilemma**.** However, the evaluation process for this disease is inefficient. In the US, patients with symptoms of chest pain are generally evaluated in an ED. As a result, EDs care for 8-10 million patients annually with a complaint of chest pain.[^2^](#_ENREF_2)^,^ [^3^](#_ENREF_3) Of all patients presenting with chest pain, almost two thirds will be admitted to the hospital, but only 10% of these patients are ultimately diagnosed with an acute coronary syndrome (ACS).[^4-7^](#_ENREF_4) This over-triage has been estimated to cost $10-13 billion annually.[^8-10^](#_ENREF_8) Excessive admissions also contribute to hospital and ED crowding, which has been linked to an overall decrease in quality of care.[^11^](#_ENREF_11)^,^ [^12^](#_ENREF_12) This inefficiency also taxes the US in other ways such as lost productivity for affected patients and unnecessary invasive procedures. Equally important, this inefficiency consumes resources that could be diverted for other health interventions.

The evaluation of chest pain is also notoriously difficult for physicians. Despite a high rate of admissions for patients with chest pain, up to 4% of patients with acute myocardial infarction are inappropriately discharged from the ED.[^4^](#_ENREF_4) These patients, inadvertently discharged home with ACS, have higher mortality compared to those hospitalized[^4^](#_ENREF_4), emphasizing the importance of making the correct diagnosis the first time. Thus, physicians have adopted a strategy of admitting most patients with chest pain to observation units or inpatient beds for lengthy evaluations to avoid missing ACS. These practices lead to lengthy hospital stays, exacerbating hospital crowding, and increasing cost.

In response to this issue, a decision aid, called the HEART score was designed to risk stratify patients with chest pain or related symptoms without stress testing or cardiac imaging. It has five

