## F4. Missing Outcome Data

Based on prior studies we expect >90% to have complete follow-up data from the EMR or phone follow up calls. Participants without follow up data will be searched for the Social Security Death Master File. Those with missing outcome data will be treated as censored and will be considered to have not had a safety event. A planed sensitivity analysis will be used to test this assumption.

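### F2's precision claim fails under the interval fixed in F3: 50 MACE events with 98% observed sensitivity give an exact 95% lower bound of 89.4%, not above 90%.

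*Protocol*

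**What the plan says.** Section F2 sets the aim: "we hope to demonstrate that paramedics are able to achieve 98% sensitivity for the detection of MACE". It then gives the precision requirement and the number of events: "with a lower bound of the 95% confidence interval that exceeds 90% we will need at least 50 patients with MACE events". The step to the total is "Assuming a 10% MACE rate among our chest pain population", so that "to include 50 patients with adverse events we will need a total sample size of 500 patients".

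F2 names no method for the interval. Section F3 does, directly after listing sensitivity and the other accuracy measures for MACE: "Corresponding 95% exact binomial confidence intervals will be computed". No other interval method for a proportion appears in the protocol, and neither section mentions a one-sided bound.

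**The concern.** F2 states a threshold: at 98% sensitivity, 50 events are enough to put the lower 95% limit above 90%. Whether that is true depends only on the interval method, and F3 supplies one. If the threshold fails under that method, the protocol's only sample-size justification contains a false statement about the precision of its first primary hypothesis (A2).

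A reader would take from F2 that a study performing as planned, with one MACE missed in 50, will report a lower limit above 90%. F1 says that favourable results would support using the score to change prehospital care and transport plans, so whoever reads the result should know beforehand what precision the design can give.

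**Working it through.** **Inputs.** Target sensitivity 98% (F2). Required lower limit above 90% (F2). Confidence level 95%, exact binomial (F3); taken as two-sided, which is the usual meaning of an unqualified 95% interval. Events 50, MACE rate 10%, total 500 (F2).

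**Step from events to patients.** 50 / 0.10 = 500. F2's total follows correctly from its number of events.

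**Exact interval at the planned result.** 98% of 50 is exactly 49, so no rounding is involved. The exact (Clopper-Pearson) lower limit for x of n is the p that solves P(X ≥ x | n, p) = 0.025, which is the 0.025 quantile of Beta(x, n − x + 1). The upper limit is the 0.975 quantile of Beta(x + 1, n − x).

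- Lower limit for 49/50: 0.8935.
- Upper limit for 49/50: 0.9995.

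The interval is 89.35% to 99.95% (89.4% to 99.9% as reported in the working figures). The lower limit is 90 − 89.35 = 0.65 percentage points short.

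**Direct check at 90%.** If true sensitivity were 0.90, then P(X ≥ 49 | 50, 0.90) = 50 × 0.90^49 × 0.10 + 0.90^50 = 0.0286 + 0.0052 = 0.0338. This is above 0.025, so 90% lies inside the interval.

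**What clears 90%.**

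| Missed MACE | Largest number of events that fails | Lower limit | Smallest number that passes | Lower limit |
|---|---|---|---|---|
| 0 | 35 (35/35) | 0.89997 | 36 (36/36) | 0.9026 |
| 1 | 53 (52/53) | 0.8993 | 54 (53/54) | 0.9011 |
| 2 | 69 (67/69) | 0.8992 | 70 (68/70) | 0.9006 |

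At exactly 50 events only 50/50 passes: 0.025^(1/50) = 0.929.

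**Can the 50 be reproduced another way?** Lower limits at 49/50 by other methods:

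| Method | Lower limit | Above 90%? |
|---|---|---|
| Exact, two-sided (F3) | 89.4% | no |
| Wilson | 89.5% | no |
| Agresti-Coull | 88.5% | no |
| Mid-P | 90.5% | yes |
| Exact, one-sided 95% | 90.9% | yes |
| Jeffreys | 91.0% | yes |
| Wald | 94.1% | yes |

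The methods that pass are not named in the protocol. None tried gives 50 as its natural minimum: with one miss, for example, the one-sided exact bound already passes at 46 events.

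**Chance of a bound above 90% at a true sensitivity of 98%.** With exactly 50 events this is the chance of no miss: 0.98^50 = 0.364. With the number of events varying as Bin(500, 0.10), averaging over that distribution gives 0.470. With exactly 54 events it is the chance of at most one miss, 0.706.

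**The case against.** The best defence is that F2 names neither a method nor a side, and that 50 events do suffice under several intervals in common use, as the table shows. The shortfall is 4 events in a study that calls itself a pilot, F2 speaks of a minimum of 50, and F3 will report whatever interval the data give. The point about size stands and lowers the weight of the finding. The point about method does not rescue the sentence: F3 names exact binomial intervals for this very quantity, and a precision statement should describe the interval that will be reported.

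Three stronger readings are tempting, and the documents do not support them.

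- A reader might infer that the study is likely to fail its primary criterion, given the 36% to 47% above. But A2 and Aim 2 ask for 98% sensitivity and negative predictive value, and no section makes a lower bound above 90% a condition of success. F2 also claims no power or assurance; it describes precision at an expected estimate. These chances are useful context, not evidence of a second error.
- A reader might infer that loss to follow-up cuts the expected events from 50 to 45. F4 does say "Based on prior studies we expect >90% to have complete follow-up data from the EMR or phone follow up calls", and F2 makes no allowance for loss. But F4 keeps patients with missing outcomes in the analysis as having no event, and E1 counts any event found on record review even when the patient cannot be reached. Index-visit events come from the receiving hospital's own records. Loss therefore removes only later events that no source captures, and 45 would require a tenth of all MACE to disappear.
- A reader might infer that the 10% rate is too high, because B1 says "almost two thirds will be admitted to the hospital, but only 10% of these patients are ultimately diagnosed with an acute coronary syndrome". That sentence is ambiguous about which patients it means. It also concerns a diagnosis of acute coronary syndrome, whereas MACE here includes coronary revascularization and could be more or less frequent. The protocol gives no basis for putting a different rate in F2.

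**Conclusion.** F2 is wrong as written. Under the exact interval fixed in F3, read as two-sided, 98% sensitivity in 50 events has a lower 95% limit of 89.4%, so the stated bound is not reached at the stated size. One missed MACE needs at least 54 events; 50 events suffice only with no miss.

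The error is small: 0.65 percentage points on the bound, or 4 events, which is about 40 patients at the protocol's 10% rate (4 / 0.10). It does not undermine the design, the choice of 500 or the planned analysis. It should be fixed, since it sits in the only sample-size rationale and is easily corrected, but it is not a reason to hold up the study. The conclusion rests on the two-sided reading of a 95% interval and on F3's method also applying to F2; it does not depend on the event rate or on follow-up.

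**What to change.** Keep N = 500 and replace the precision sentence in F2 with wording such as:

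> With 50 MACE events (expected at a 10% rate in 500 patients) and an observed sensitivity of 98% (49/50), the exact 95% CI is 89.4% to 99.9%. A lower bound above 90% requires no miss in at least 36 events, at most one in at least 54, or at most two in at least 70.

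Optionally add that, at a true sensitivity of 98%, the chance of a bound above 90% is about 36% with exactly 50 events, and about 47% when the number of events varies as Bin(500, 0.10).

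If the sponsor prefers to keep the claim of a bound above 90% with one miss, the target has to be at least 54 events, about 540 patients at a 10% rate (54 / 0.10).

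The first option costs protocol wording only, with a slightly less favourable statement of precision and no extra patients or change to the analysis. The second costs about 40 more patients.
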